## Abstract

**Introduction::**

Out-of-hospital cardiac arrest (OHCA) remains a major cause of mortality in the UK, with survival rates remaining low despite advancements in resuscitation techniques. The European Resuscitation Council and Resuscitation Council UK guidelines recommend controlled ventilation during cardiopulmonary resuscitation (CPR), yet studies show that ambulance clinicians often fail to meet these standards. In particular, hyperventilation has been linked to worse outcomes. This protocol describes a study that will explore the impact of different applications of real-time ventilation feedback on the quality of ventilations during CPR in a simulated environment.

**Methods::**

This exploratory simulation study will assess the effectiveness of real-time feedback on the quality of ventilations delivered by ambulance clinicians. Participants from North East NHS Foundation Trust will be randomly assigned to three arms, receiving a single episode of feedback, regular feedback or no feedback (used as a control group). Each arm will complete four simulated OHCA scenarios over six months, and their ventilation quality will be assessed at each session. The primary outcome will be the quality of ventilations, measured by rate and tidal volume, at the six-month mark. Secondary outcomes include trends in ventilation quality over time and participant characteristics.

**Discussion::**

This study aims to explore whether regular feedback improves the quality of ventilations during CPR and whether feedback sessions influence skill retention over a six-month period. Findings could inform training strategies, highlighting the role of real-time feedback in maintaining high-quality CPR skills. With a lack of prior research on ventilation skill maintenance in the UK, this study is expected to provide valuable insights into optimising clinical performance.

## Introduction

Out-of-hospital cardiac arrest (OHCA) is the sudden cessation of effective circulation due to absence of cardiac pump function in an out-of-hospital setting (Myat et al., 2018). In the UK in 2023, National Health Service (NHS) ambulance services treated approximately 29,625 OHCAs, with a low survival rate of 9% (Warwick University OHCAO Project, 2023). When treating an OHCA, ambulance clinicians are required to deliver chest compressions and manual ventilations as part of cardiopulmonary resuscitation (CPR). Adequate ventilation is an important aspect of CPR (Olasveengen et al., 2017). Hyperventilation is a critical issue that has received little attention, despite its association with increased intrathoracic pressure and impaired haemodynamics and cardiac output, as well as cerebral vasoconstriction, which can significantly reduce brain perfusion (Kirk et al., 2023). Ultimately, hyperventilation during CPR can be deleterious to survival (Aufderheide & Lurie, 2004; Pitts & Kellermann, 2004).

The European Resuscitation Council (ERC) adult advanced life support (ALS) guidelines recommend ventilating cardiac arrest patients at a rate of 8–12 ventilations per minute with a tidal volume sufficient to produce chest rise (Soar et al., 2021). A previous version of these guidelines specified a tidal volume of 500–600 ml and warned against hyperventilation (Soar et al., 2015). These recommendations are largely mirrored by the Resuscitation Council UK guidelines (Resuscitation Council UK, 2021) and UK ambulance service guidelines (JRCALC, 2023). Despite this, research suggests that 80% of caregivers hyperventilate cardiac arrest patients (Nehme & Boyle, 2009). Previous research has shown that compliance with ventilation guidelines can be improved by the use of feedback (Khoury et al., 2019), in the same way that real-time feedback has improved the quality of compressions. There is currently a lack of data surrounding the use of real-time ventilation feedback devices in OHCA and until very recently it has not been possible to measure the quality of ventilations (Drennan et al., 2024).

A recent manikin study by Charlton et al. (2021) identified that ambulance clinicians delivered poor-quality ventilations, such as hyperventilation or hypoventilation, in respect to both the tidal volume and ventilation rate. The Charlton et al. study showed that many clinicians did not meet ERC guidelines without feedback, but that when feedback was provided, compliance with ERC guidelines significantly improved.

Ventilation with a bag-valve-mask (BVM) is a skill used by ambulance clinicians globally. The JRCALC advanced life support guidelines states: ‘*The initial approach to airway management should usually be BVM*’ (JRCALC, 2023), which aligns with Resuscitation Council ALS guidelines that state: ‘*During CPR, start with basic airway techniques and progress stepwise according to the skills of the rescuer until effective ventilation is achieved*’ (Resuscitation Council UK, 2021). The American Association of EMS Physicians (NAEMSP) recently published a position statement stating that BVM is: ‘*a fundamental airway management skill for all Emergency Medical Services (EMS) clinicians*’ (Lyng et al., 2022). However, the American Heart Association cautions: ‘*BVM is a challenging skill that requires considerable practice for competency*’ (Kleinman et al., 2015).

Outside of clinical practice, ventilation competency, including use of the BVM, is delivered through infrequent training sessions. Unless an individual seeks out relevant activities or completes refresher training provided by their organisation, which is often delivered on an infrequent basis, their skills are likely to decay (Woodman et al., 2021). An initial literature search failed to identify any literature on the maintenance of BVM skills by UK paramedics, although there is literature on other airway skills and maintenance from other settings, such as completing high-fidelity simulation to maintain endotracheal intubation competency (Pilbery, 2018; Youngquist et al., 2008).

If we accept that BVM ventilation is a core ambulance clinician skill, that competence fades over time and that clinicians receive little refresher training or feedback, then it is unsurprising that studies have shown that clinicians struggle to ventilate with a BVM according to guidelines (Charlton et al., 2021; Khoury et al., 2016). However, studies have also shown that real-time feedback can improve the ability of clinicians to ventilate according to guidelines (Charlton et al., 2021; Khoury et al., 2016), but what the impact of occasional or regular access to feedback would be remains unclear.

The NHS ambulance services resuscitate around 30,000 patients with cardiac arrest annually (Perkins et al., 2015; Warwick Clinical Trials Unit, 2021), and a BVM will be used in most of these cases. A BVM will also be used in treatment of other conditions, such as respiratory arrest, so the number of cases where a BVM is used will be higher than 30,000. Therefore, exploring what impact occasional feedback, regular feedback and the current standard of no feedback has on BVM skill maintenance is potentially very important.

### Aims and objectives

The aim of this project is to explore the impact of different applications of real-time ventilation feedback on ambulance clinicians’ ability to deliver high-quality ventilations during CPR in a simulated setting and to explore if skills change over a six-month period.

**Primary objective:** The primary objective of this project is to explore the impact of a single session of feedback compared with regular feedback and no feedback on ventilation quality.

**Secondary objective:** The secondary objective of this project is to explore whether ventilation skills change over a six-month period with repeated assessment.

## Methods

### Trial design and setting

The study will use a randomised experimental design. This study is exploratory in nature and will use a simulated OHCA scenario and volunteer clinicians from a single NHS ambulance service. Participants will be randomised 1:1:1 to three arms:

Ventilation feedback at the first session only (single feedback)Ventilation feedback at all sessions (regular feedback)No feedback (control arm).

This study will be conducted by arranging study sessions at sites across the North East NHS ambulance service and inviting participants to complete the scenario at the appropriate time (months 0, 2, 4 and 6) (Table 1). Multiple dates will be arranged to facilitate participation.

**Table 1. table1:** Summary of the study structure.

	Session 1 (month 0)	Session 2 (month 2)	Session 3 (month 4)	Session 4 (month 6)
**Regular feedback**	Feedback	Feedback	Feedback	Feedback
**Single feedback**	Feedback	No feedback	No feedback	No feedback
**Control**	No feedback	No feedback	No feedback	No feedback

The scenarios will be delivered in a standardised manner, using the same equipment each time. Each scenario will last approximately six minutes, which equates to approximately three two-minute cycles of CPR. Where it is not possible to include pairs of participants, a member of the research team may have to perform the chest compressions. Each study session should last less than one hour per participant, which will include a briefing session, the actual simulation and a debrief period with the participants.

### Randomisation procedure

A pre-generated randomisation will be used, with participants allocated sequentially when they attend session 1 at month 0.

### Eligibility criteria

Any operational ambulance staff (paramedics and non-paramedics) employed by North East NHS ambulance service who use a BVM to ventilate as part of their role will be eligible to participate.

### Sample size

This is an exploratory study, so there is no formal sample size or power calculation. The study will use a mix of sampling methods, with one group being a non-probability convenience sampling and a sub-group being sampled via purposive sampling.

The study will aim to recruit between 18 and 30 participants from North East NHS ambulance service operational ambulance staff. This target was selected for pragmatic reasons and the resources available for the study. If more than 30 participants volunteer, it will be the first 30 staff who are included. Up to 40 North East NHS ambulance service Hazardous Area Response Team (HART) paramedics will be offered the chance to participate in the study, but will be analysed as a sub-group in addition to the main analysis. The HART group will be analysed as a separate sub-group due to the participants having different baseline characteristics, such as their training.

### Participant recruitment

Participants will be recruited via North East NHS ambulance service internal media, social media and personal contacts. Participants will be asked to complete a consent form prior to study participation after they have had sufficient time (>24 hours) to consider the participant information. Consent will be checked at the start of each session.

Participants who complete all four study sessions will receive a CPD certificate and a £25 gift voucher in appreciation for their time and input. Participants will also be offered the chance to receive individualised feedback based on the study data and a copy of the final study results.

### Interventions

The Zoll AccuVent real-time feedback device is an adjunct placed between the supraglottic airway device or endotracheal tube (ETT) and the catheter mount (all standard pieces of equipment used by North East NHS ambulance service clinicians when managing an airway), which is attached to the Zoll defibrillator as in Figure 1. The Zoll AccuVent provides visual feedback, displaying the rate and tidal volume of each ventilation in the form of a pictorial guide of a circle that fills during each ventilation, and has the capacity to record and download data following each use.

**Figure fig1:**
[figure not shown]
Figure 1. Zoll AccuVent real-time feedback device.

The visual displays are colour coded to ease interpretation (Figure 2). The Zoll AccuVent real-time feedback device is similar to the chest compression feedback provided by the Zoll defibrillators already used in the North East NHS ambulance service and which is familiar to clinicians.

**Figure fig2:**
[figure not shown]
Figure 2. Zoll AccuVent visual feedback.

### Outcomes

The primary outcome for this study will be the quality of the ventilations measured by a combination of rate and volume at month 6 compared between the three arms of the study. Primary outcome data will be tested using either a one-way ANOVA or Kruskal-Wallis test, depending on the distribution (normality) of the data.

Descriptive data will also be reported on secondary outcomes, including:

trends in ventilation qualityparticipants factors, including: age; sex; job role; any recent CPR/ventilation training received; prior involvement in the VANZ1 or VANZ2 studies (previous studies that form the knowledge base for this study conducted by the study team (Charlton et al., 2021)); and recent experiences of delivering ventilations in practice.

As scenarios may be repeated with pairs of participants, we will also look at whether there is a difference between people who provide ventilations first or second.

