### Data analysis

Data will be collected in Excel, and SPSS will be used for statistical analysis. Primary outcome data will be tested using either a one-way ANOVA or Kruskal-Wallis test depending on the distribution (normality) of the data. Descriptive data will also be reported on secondary outcomes. The HART participants will be analysed as a sub-group using the same statistical analysis due to the participants having a different skill set and cardiac arrest exposure compared to the rest of the participants.

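### The stated primary analysis is a three-arm omnibus test chosen by normality, which gives no direction or size for the single-versus-regular and single-versus-none contrasts in the primary objective

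*Protocol article*

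**What the plan says.** In the protocol article, Aims and objectives sets the primary objective as to "explore the impact of a single session of feedback compared with regular feedback and no feedback on ventilation quality". Trial design and setting states: "Participants will be randomised 1:1:1 to three arms".

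Outcomes defines the primary outcome as ventilation quality, from rate and volume combined, compared between the three arms at month 6. It then fixes the analysis: "Primary outcome data will be tested using either a one-way ANOVA or Kruskal-Wallis test, depending on the distribution (normality) of the data". Data analysis repeats that these data will be "tested using either a one-way ANOVA or Kruskal-Wallis test depending on the distribution (normality) of the data" and applies the same analysis to the HART sub-group. Secondary outcomes are to be reported descriptively. The article mentions no pairwise contrast, effect estimate or confidence interval.

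On numbers, Sample size says "The study will aim to recruit between 18 and 30 participants" and declares "This is an exploratory study, so there is no formal sample size or power calculation". Up to 40 HART paramedics "will be offered the chance to participate in the study, but will be analysed as a sub-group in addition to the main analysis".

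**The concern.** The objective names two comparisons centred on the single-feedback arm: against regular feedback and against none. A one-way ANOVA or Kruskal-Wallis test asks a different question, namely whether the three arms are all alike. A significant result does not say which arm differs, in which direction or by how much. A non-significant result carries no statement of the effects that remain plausible.

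What is at stake is the use of the findings. The abstract's Discussion says they could inform training strategies. That one session is as good as regular feedback and that one session leaves nothing by month 6 are opposite conclusions for training, and the stated p-value can look the same under both.

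The choice between ANOVA and Kruskal-Wallis also depends on the outcome data. No criterion is given, and the two tests compare different things (means or ranks).

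**Working it through.** **Inputs.** From the article: three arms, 1:1:1, 18 to 30 people in the main group, so 18/3 = 6 to 30/3 = 10 per arm before dropout. Assumed, because the article gives no value: two-sided alpha 0.05, effects in SD units, normal errors with equal variance, and a quality score where higher is better. The plan states no power or effect size, so there is no figure of its own to reproduce.

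**1. Can the omnibus test tell the two answers apart?** Take a 1.5 SD effect and list the arm means as (control, single, regular).

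- A, single equals control: (0, 0, 1.5). Grand mean 0.5; squared deviations 0.25 + 0.25 + 1.00 = 1.50.
- B, single equals regular: (0, 1.5, 1.5). Grand mean 1.0; squared deviations 1.00 + 0.25 + 0.25 = 1.50.

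In both, f² = 1.50/3 = 0.50, so f = 0.707. The noncentrality N·f² is 18 × 0.50 = 9 or 30 × 0.50 = 15. ANOVA power depends on the means only through this quantity, so it is the same in A and B.

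| Per arm | Power from noncentral F (A and B) | Simulated, A | Simulated, B |
|---|---|---|---|
| 6 | 0.677 | 0.682 | 0.684 |
| 10 | 0.916 | 0.925 | 0.918 |

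The simulations used 3,000 runs per setting. The same symmetry holds for Kruskal-Wallis under these assumptions, because relabelling the arms and reversing the scale leave its statistic unchanged.

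**2. Would pairwise intervals tell them apart?** With the pooled variance, the 95% half-width is t(0.975, 3(n−1)) × √(2/n):

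- n = 6: 2.131 × 0.577 = 1.23 SD
- n = 10: 2.052 × 0.447 = 0.92 SD

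Centring each interval on the true difference gives:

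| Contrast | A, n = 6 | B, n = 6 | A, n = 10 | B, n = 10 |
|---|---|---|---|---|
| Single − control | −1.23 to 1.23 | 0.27 to 2.73 | −0.92 to 0.92 | 0.58 to 2.42 |
| Single − regular | −2.73 to −0.27 | −1.23 to 1.23 | −2.42 to −0.58 | −0.92 to 0.92 |

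The intervals are wide, but their pattern differs between A and B, where the omnibus rejection rate does not.

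**3. How well does a normality check work here?** The article names no test, so Shapiro-Wilk at 0.05 is assumed. For lognormal data with sigma 0.5, it detects the skew in 13% (n = 6) to 25% (n = 10) of samples when applied to one arm. Applied to the pooled residuals of all 18 to 30 people, it detects it in 29% to 59%. For exponential data on pooled residuals the rates are 50% to 83%. The check is unreliable at the lower end but not useless.

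**4. Does the switch damage the error rate?** With the gated procedure (Shapiro-Wilk on residuals, then ANOVA or Kruskal-Wallis) under a lognormal null with sigma 0.5, simulated type I error is 5.4% at 6 per arm and 5.2% at 10 per arm. The harm is small, and what remains is that the target of comparison is not fixed in advance.

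**The case against.** **A condensed article may leave follow-up comparisons to a full protocol or analysis plan.** This is the strongest objection. A reader might infer that the plan rules out pairwise comparisons; the text does not support that, because naming an omnibus test does not exclude them. What stands is narrower: the article fixes the primary analysis twice, and what it fixes does not deliver the contrasts in its own objective.

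**The omnibus test matches the outcome as worded, a comparison between three arms.** True, and it answers part of the objective. It does not answer how the single session compares with each alternative.

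**Unequal variances.** A reader might infer that the regular arm, guided towards a target, will vary less, and that error rates would then reach 9 to 10%. The article gives no SD or variance ratio, so the smaller variance is an assumption. Even with that arm's SD set at 0.3 to 0.5 of the others, 9 to 10% arises only for an unadjusted pooled contrast made without the omnibus test first, which the plan does not specify. The planned omnibus ANOVA stays at about 5.5 to 6.3%, and a single-versus-control contrast made after a significant omnibus test at about 4.7 to 5.7%.

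**Low power.** A reader might also count the small sample as a fault here. The article openly calls the study exploratory, with no power calculation and a size set for pragmatic reasons. Pairwise intervals would be imprecise too.

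**HART staff.** The 6 to 10 per arm is the main group only. The wording leaves some doubt whether HART staff also enter the main analysis, but the missing contrasts do not depend on the sample size.

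**Conclusion.** The concern holds as a mismatch between objective and stated analysis. The omnibus test cannot separate the two answers the objective needs: at a 1.5 SD effect it rejects about 68% (6 per arm) or 92% (10 per arm) of the time under either. The equality follows from the symmetry of the test; the percentages rest on the assumed alpha, effect size and equal-variance normal model.

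The normality-based switch is secondary. It lets the data choose between means and ranks, with limited ability to see skew at 18 to 30 people, but it moved type I error little in the case checked.

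The documents do not support adding that error rates are seriously inflated, that the regular arm will be less variable, or that low power is a defect of this analysis. The study can run as designed. The change is worth making because it is cheap and brings the primary result into line with the primary question.

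**What to change.** In Outcomes and Data analysis, name as the primary result the month-6 differences single versus control and single versus regular, with regular versus control alongside. Give each a 95% confidence interval that allows unequal variances, for example Welch. Keep one omnibus test chosen in advance, such as Kruskal-Wallis or a permutation test, as support, and delete the choice by normality. Use the same wording for the HART sub-group.

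State whether the intervals are adjusted for multiplicity. Three unadjusted 5% comparisons carry a family-wise error of about 1 − 0.95³ = 0.143 (independence approximation). Bonferroni would widen the pooled half-widths from 1.23 to 1.56 SD at 6 per arm and from 0.92 to 1.14 SD at 10 per arm. Unadjusted intervals, labelled as such, are defensible in an exploratory study.

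The cost is wording only; design, recruitment and data collection are untouched. Separate-variance intervals are slightly wider. With equal sample variances, Welch has 2(n−1) degrees of freedom, giving 2.228 × 0.577 = 1.29 SD at 6 per arm and 2.101 × 0.447 = 0.94 SD at 10 per arm. Several estimates are reported in place of one p-value.

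### Pairing individually randomised participants may let control and single-feedback participants watch a partner's ventilation feedback, diluting mainly the single-feedback versus control contrast

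*Protocol article*

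**What the plan says.** Trial design and setting fixes individual allocation: "Participants will be randomised 1:1:1 to three arms". Randomisation procedure adds how it is carried out: "A pre-generated randomisation will be used, with participants allocated sequentially when they attend session 1 at month 0". Two people who arrive and work together would thus take their arms from separate entries on the list.

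Pairs are the normal arrangement and a researcher is the fallback: "Where it is not possible to include pairs of participants, a member of the research team may have to perform the chest compressions". The Outcomes section expects that both members of a pair may take a turn at ventilating ("As scenarios may be repeated with pairs of participants"), and plans one look at this, a comparison of first with second ventilators.

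Under Interventions, the feedback is a colour-coded picture of rate and tidal volume, produced by an adjunct connected to the defibrillator. The text describes it as "similar to the chest compression feedback provided by the Zoll defibrillators" that staff already know. Table 1 gives the control arm no feedback at any session and the single-feedback arm none after session 1, while the regular arm has it at every session, including month 6.

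Two further statements bear on the point. Each study session includes "a briefing session, the actual simulation and a debrief period with the participants", and under Participant recruitment participants are "offered the chance to receive individualised feedback based on the study data".

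**The concern.** The intervention is information on a screen, and the control condition is its absence. Both can be in the same room at the same time. While one member of a mixed pair ventilates with feedback, the other is beside the same defibrillator doing compressions, and may then take the next turn as a participant who is meant to have had no feedback.

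At stake is the primary objective, which is to compare single, regular and no feedback. A control participant who has watched one session of a partner's display has come some way towards the single-feedback condition. A single-feedback participant who watches a regular-arm partner at month 2 or 4 has come some way towards repeated exposure. A small difference at month 6 would then have two explanations, little benefit from feedback or leakage between arms, and the analysis could not separate them. The planned order comparison does not help, because exposure depends on the partner's arm as well as on who went first.

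**Working it through.** The protocol gives no power calculation, effect size or standard deviation, so there is no stated figure to reproduce. The figures below illustrate how often mixed pairs would arise and what a loss of effect would mean.

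**Inputs from the protocol.** Main group N = 18 to 30 (Sample size); 1:1:1 allocation (Trial design and setting), hence k = N/3 = 6 to 10 per arm; feedback schedule from Table 1.

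**Assumptions.** Everyone is paired, partners are drawn at random from the whole group, and arms are exactly equal.

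**1. Control participant with a feedback-arm partner at session 1.** Both other arms have feedback, so the probability is 2k/(N-1).
- N = 18: 12/17 = 0.71
- N = 30: 20/29 = 0.69

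**2. Control or single-feedback participant with a regular-arm partner at a given later session.** The probability is k/(N-1).
- N = 18: 6/17 = 0.35
- N = 30: 10/29 = 0.34

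**3. At least once over sessions 2 to 4, with a new random partner each time.** 1 - (1 - p)^3.
- N = 18: 1 - (11/17)^3 = 0.73
- N = 30: 1 - (19/29)^3 = 0.72

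**4. Control participant, at least one feedback-arm partner over all four sessions.**
- New partners: 1 - (5/17)(11/17)^3 = 0.92 and 1 - (9/29)(19/29)^3 = 0.91
- Fixed partners: 0.71 and 0.69, as in step 1

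**5. Exposure just before the participant's own turn in the same session.** The partner must also ventilate first. If order is even (an assumption), halve the figures.
- Session 1, control: 0.71/2 = 0.35 and 0.69/2 = 0.34 to 0.35
- Month 6, control or single feedback: 0.353/2 = 0.18 and 0.345/2 = 0.17

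**6. What dilution would do.** Pairwise power by the normal approximation, two-sided 5%, is Φ(d(1 - c)/√(2/n) - 1.96), where d is the true effect in SD units and c the share of it lost. Both d = 1.2 and the values of c are assumptions.

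| n per arm | c = 0 | c = 25% | c = 50% |
|---|---|---|---|
| 10 | 0.77 | 0.52 | 0.27 |
| 6 | 0.55 | 0.34 | 0.18 |

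For example, n = 10 and c = 25%: 0.9/√0.2 = 2.01, less 1.96 is 0.05, and Φ(0.05) = 0.52.

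Steps 1 to 5 are probabilities of a partner's arm or turn. They do not convert into a value of c, because the protocol gives no basis for how much a watcher learns or retains.

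**The case against.** The strongest reply is that much of this is inferred. The protocol does not say where the monitor stands, whether compression feedback is on during the scenarios, or that the compressor can see the ventilation display. The two figures that might show this are not in the text available. Pairing rules, screening and turn order may sit in a full protocol that a journal article condenses. Role swapping is stated only as something that may happen. All of this stands, so the claim is that participants *may* be exposed, not that they are.

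The random-pairing model is also idealised. Sessions run at several sites and dates, and researchers may do some of the compressions. That makes the percentages approximate, but it does not remove mixed pairs: under 1:1:1 allocation of successive arrivals, two unrelated list entries differ in arm about two times in three.

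Three stronger inferences are tempting, and the text does not support them.
- **Debriefs and individualised feedback as established leaks.** The content of the debrief is not described. The feedback offer follows the reward for completing all four sessions and is made together with a copy of the final results, so it reads most naturally as an end-of-study offer.
- **Regular versus control as equally affected.** Having watched someone else's display earlier is not equivalent to live feedback on one's own ventilations.
- **Leakage that wipes out the effect.** Nothing in the document supports a size of that order, and exposure at earlier sessions matters at month 6 only so far as it is retained over two months or more.

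The study is also declared exploratory. That lowers the demand for power, but not the need for arms that differ as intended.

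**Conclusion.** The concern holds as a design risk. Followed as written, individual allocation on arrival combined with pairs by default makes mixed-arm pairs the expected outcome, at roughly 70% for a control participant at session 1 and 35% for a control or single-feedback participant at each later session, given random pairing of everyone in equal arms. No stated rule separates the arms within a pair.

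The expected direction is towards no difference, mainly for single feedback versus control. The amount cannot be derived from the protocol. With 6 to 10 per arm there is little room for it: under the assumed 1.2 SD effect, losing a quarter would take pairwise power from 0.77 to 0.52 at 10 per arm. Exposure that has occurred cannot be undone at analysis, so this is worth settling before session 1. If screening or same-arm pairing is already laid down in the full protocol, confirming it would close the main part of the point.

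**What to change.** - At all sessions, screen the ventilation display so that only a ventilator allocated to feedback at that session can see it. Alternatively, when a pair is mixed-arm, use the research-team compressor that the protocol already permits and keep the partner out of the room until their own turn.
- Pair within arm where scheduling allows from session 2. This cannot be arranged for session 1, because arms are known only on arrival, so screening or the researcher compressor has to carry that session.
- Set at random who ventilates first, and say so.
- Record the partner's arm and the order at every session, so that any remaining exposure can be described alongside the first-versus-second comparison.
- As a precaution, state that ventilation performance data stay out of debriefs and that individualised feedback is released only after session 4, in all arms.

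The cost is a cover for the display, one extra data field, and some more researcher-performed compressions. With 6 to 10 per arm spread over several sites and dates, same-arm pairs will often not be available, so screening is the more dependable of the options. No extra visits are needed.
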